# A tailored implementation intervention to implement recommendations addressing polypharmacy in multimorbid patients: study protocol of a cluster randomized controlled trial

**DOI:** 10.1186/1745-6215-14-420

**Published:** 2013-12-05

**Keywords:** Guideline, Implementation, Knowledge transfer, Polypharmacy, Primary care, Tailored intervention

## Abstract

**Background:**

Multimorbid patients frequently receive complex medication regimens and are at higher risk for adverse drug reactions and hospitalisations. Managing patients with polypharmacy is demanding, because it requires coordination of multiple prescribers and intensive monitoring. Three evidence-based recommendations addressing polypharmacy in primary care are structured medication counselling, use of medication lists and medication reviews to avoid potentially inappropriate medication (PIM). Although promising to improve patient outcomes, these recommendations are not well implemented in German routine care. Implementation of guidelines is often hindered by specific “determinants of change”. “Tailored” interventions are designed to specifically address previously identified determinants. This study examines a tailored intervention tto implement the aforementioned recommendations into German primary care practices. This study is part of the European Tailored Interventions for Chronic Diseases project, which aims at contributing knowledge about the methods used for tailoring.

**Methods/Design:**

The study is designed as a cluster randomized controlled trial with primary care practices of general practitioners (GPs) who are organized in quality circles. Quality circles will be the unit of randomization with a 1:1 ratio. Follow-up time is 6 months. GPs and healthcare assistants in the intervention group will receive training on medication management. Each GP will create a tailored concept of how to implement the three recommendations into his/her practice. Evidence-based checklists for medication counselling and medication reviews will be provided for physicians. A tablet PC with an interactive educational tool and information leaflets will be provided for use by patients to inform about the necessity of continuous medication management. Control practices will not receive special training and will provide care as usual. Primary outcome is the degree of implementation of the three recommendations, which will be measured using a prespecified set of indicators. Additionally, the PIM prescription rate, patient activation, patients’ beliefs about medicine, medication adherence and patients’ social support will be measured.

**Discussion:**

This study will contribute knowledge about the feasibility of implementing recommendations for managing patients with polypharmacy in primary care practices. Additionally, this study will contribute knowledge about methods for tailoring of implementation interventions.

**Trial registration:**

Clinicaltrials.gov
ISRCTN34664024

## Background

An increasing number of patients have multiple chronic conditions
[1]. Multimorbidity is associated with an increased likelihood of complex medication regimens often consisting of five or more different drugs, commonly defined as polypharmacy
[2]. With administration of increasing numbers of drugs, the risk of adverse drug reactions (ADRs) increases substantially
[3] thereby causing potentially avoidable hospital admissions
[4] and preventable deaths
[5]. Managing multimorbid patients with polypharmacy is particularly demanding in primary care practices (PCPs), as it requires coordination of multiple prescribers, profound pharmacological knowledge and intense monitoring of patients.

### Recommendations for patients with polypharmacy

An increasing body of literature has been published regarding strategies to address polypharmacy in multimorbid patients
[6]. For the Polypharmacy in Multimorbid Patients (PomP) study, three core recommendations derived from the literature have been identified. German guidelines for polypharmacy in primary care, which were published after we made this selection, refer to these recommendations
[7].

(1) Recommendation 1/structured medication counseling (SMC): all patients with polypharmacy and additional risk factors for medication problems should receive SMC at least once per year. In addition to medication-related information, SMC comprises a complete inventory of the medications actually taken (a so-called “brown bag review”) and assessment of patient adherence and possible application problems. A separate appointment should be planned for SMC
[8].

(2) Recommendation 2/consequent use of medication lists: All patients with polypharmacy should take along an updated, complete (that is, containing all necessary information) and comprehensible medication list
[7,9].

(3) Recommendation 3/medication reviews to reduce potentially inappropriate medication (PIM): The appropriateness of a medication can be judged by using explicit criteria (usually drug-to-avoid lists) and implicit criteria (usually checklists). Since 2010, the PRISCUS list has been available in Germany. It lists 82 drugs as potentially inappropriate for use in older patients
[10]. The Medication Appropriateness Index (MAI) is a tool to systematically check individual medication regimens to ensure that they meet criteria such as indication, dosage, interactions and applications
[11]. It is recommended that physicians, with the aid of such tools, regularly review the medication regimens of patients with polypharmacy
[7].

### Current routine care

Implementation of these recommendations would likely improve medication management and the health status of multimorbid patients with polypharmacy
[7]. To date, however, these recommendations have not been implemented well in German routine care.

Deficiencies concerning communication between physicians and patients about their medicine are well-known, both at discharge and in ambulatory care
[12-14]. Information about medication is usually given only at the time of first prescription, and monitoring of efficacy and ADRs is often insufficient
[14]. Patients are dissatisfied with the information provided about possible side effects and feel that there is little chance to discuss their questions and concerns during the consultation
[15]. There is evidence that SMC may increase patient satisfaction
[16], improve adherence and reduce ADRs and hospitalizations
[17].

Several independent studies have shown that there are discrepancies between medication records and actual medication intake in about 75% of cases
[18-20] and that 25% of those discrepancies are potentially harmful
[21]. In a recent study, it was reported that 40% of primary care patients in Germany reported taking a mean of two drugs of which their general practitioners (GPs) were unaware
[22]. Organizational issues (for example, medication records not being updated) were the most frequent cause of differences between medication records and actual medication intake.

An analysis based on the PRISCUS list showed that 25% of the elderly received at least one PIM prescription in 2010
[23]. Medication errors, defined according to the criteria of the MAI, are frequent. An Austrian study examining the medication regimens of 169 patients with polypharmacy in 22 general practices found that, on average, 2.7 medications per patient were not indicated and that 93.5% had taken at least one non-evidence-based medication
[24].

### Healthcare system

The challenge of managing patients with polypharmacy is particularly relevant for countries without an established gatekeeping system. Germany has a strong ambulatory specialist care system in addition to primary care. Patients have free choice of doctors and do not have to be registered at any PCP. Therefore, different care providers are able to alter medication regimens without communication with the GP.

In an attempt to strengthen the coordinating role of GPs, some German health insurance policies offer GP-centred care contracts (Hausarztzentrierte Versorgung, or HzV). Patients who are voluntarily enrolled in an HzV contract agree to get a referral from a GP before they contact a specialist. Specialists who voluntarily participate in HzV are obliged to send a report to the GP after each patient contact. GPs participating in the HzV care contract of one German health insurance in one federal state in Germany (“HzV AOK Baden-Württemberg” care contract)
[25] are additionally obliged to participate regularly in quality circles (QCs)
[26], which comprise small-group meetings of GPs from one geographical region and written feedback on their individual practice patterns. Currently, there are 309 QCs in the German federal state Baden-Württemberg, each comprising on average 10.9 GPs (±5.6).

### Tailored interventions

Implementation of evidence-based practice in healthcare is often hindered by specific barriers and promoted by enablers, also referred to as “determinants of change”. Interventions designed to address previously identified determinants are often referred to as “tailored interventions”
[27]. This study is part of the tailored interventions for chronic diseases (TICD) project, which aims to contribute knowledge to gain a better understanding of methods used to tailor implementation interventions in chronic illness care
[28]. On the basis of prior work of the TICD project, the aim of the PomP study is to assess the effectiveness of a tailored implementation intervention for polypharmacy in multimorbid patients.

## Methods

### Trial design

The intent of the PomP study investigators is to improve the implementation of the aforementioned core recommendations. The aim is to assess the effectiveness of a tailored implementation intervention compared to usual care in professional practice. The study design is a two-armed cluster randomized controlled trial with QCs of PCPs with a 1:1 ratio of units of randomization (see Figure 
1). Follow-up time is 6 months.

**Figure 1 F1:**
[figure not shown]
**Trial design of the Polypharmacy in Multimorbid Patients study.** Primary care practices (PCPs) organised in quality circles (QCs) are randomized by QC level. QCs are educational meetings of PCPs from one geographic area.

### Intervention study group

The PomP study tailored intervention was developed on the basis of previously identified determinants and strategies. The result of this previous work was a standardised list of determinants for implementing into practice the three core recommendations (SMC, use of medication lists and medication reviews to reduce PIM), as well as a set of strategies addressing these determinants. An implementation intervention has been designed on the basis of this prior work. Each strategy within the implementation intervention addresses one or more specific determinants. Figure 
2 specifies which determinant is meant to be addressed by each strategy. The strategies used in the implementation interventions are outlined in the following subsections.

**Figure 2 F2:**
[figure not shown]
**Logic model of the tailored implementation intervention in the Polypharmacy in Multimorbid Patients study.** QC, quality circle; SMC, structured medication counselling.

#### Workshops

GPs and healthcare assistants (HCAs) will receive training in four main areas: (1) medication counselling; (2) medication management, including the use of medication lists; (3) pharmacological issues, including PIMs; and (4) organisational study issues, such as documentation, use of tablet PCs and creation of practice-based pathways. A half-day training session will be organised by the study team for all PCPs in the intervention group. At least one GP and one HCA from each PCP must be present. The aim of the training sessions is to increase expert knowledge of medication management.

#### Individual practice concepts

Each PCP team will create an individual concept which describes how they plan to implement the recommendations into their practice. The aim of individual practice concepts is to enhance awareness of the processes and possible performance gaps in the individual practice and to optimise management processes of the PCP by clearly defining responsibilities and tasks and by designing tailored strategies for each PCP.

#### Presentation of individual practice concepts at quality circle meetings

Each QC is obliged to organise one meeting in addition to their regular agenda, during which each practice team will present its individual implementation concept. The aim of this meeting is to increase the likelihood that practice concepts will be elaborated and to set the stage for the exchange of ideas for individual solutions among the QC participants.

#### Checklist for SMC and medication reviews

A checklist for SMC and medication reviews
[8] will be handed out to all PCPs of the intervention group and should be used to document each SMC review and each medication review. The checklist for medication reviews will be based on the components of the MAI
[11]. The aim of the checklist is to structure and thus facilitate the counselling and review process and to increase routine and quality.

#### Template for medication lists

A template for medication lists will be given to each PCP as an adaptable text file
[9]. Practice teams are supposed to make sure that the medication lists they use by default contain the information specified in the template.

#### Tablet PCs for patients

A tablet PC with an interactive educational tool for the three core recommendations for patients will be provided (one tablet PC per PCP). The tool will be available in German, English and Turkish to reach a broader spectrum of patients, including non-German-speaking patients. All patients in the target group, as defined by the previously created patient register, should complete the educational tool at least once. The aim of the tool is to increase patients’ interest in and awareness of medication-related topics and thus introduce a behaviour change that results in a higher proportion of patients carrying a medication list with them and reporting medication changes and problems proactively to GPs. Difficulties in comprehension due to language barriers will be reduced.

#### Campaign

Posters and flyers for patients with information about the three core recommendations will be provided. Flyers should be placed in the PCP waiting room and handed out to the patients in the target group. Posters should be hung on the walls in the PCP. The aim of the campaign is identical to that of the tablet PC; however, all patients visiting the practices of the intervention group will be exposed to the campaign, whereas the tablet PC tool is to be used only by a sample of patients.

Determinants identified and prioritised, but not addressed by this intervention are cognitively impaired patients, lack of resources (time, financial compensation), multiple information sources, information exchange at interfaces, compatibility of practice software, data security, rebate contracts, alternatives to PIM, discharge medication, geriatric/pharmacological consultations, easy access to PIM and entering medication data into software programs.

### Usual care study group

PCPs in the usual care group will participate in thrice-monthly QCs thematically different from those in the intervention group. They will not receive special training in medication management. These PCPs will continue to deliver care as usual within the framework of the GP-centred care contract. GPs in the control group will be informed about the three recommendations by receiving the information leaflet explaining the PomP study.

### Primary outcome

The primary outcome will be the degree of implementation of the three recommendations measured at the patient level, that is the effectiveness of the implementation program on PCP performance. This will be assessed using a set of indicators. The degree of implementation will be expressed by the number of indicators fulfilled per patient included in the study (see Table 
1).

**Table 1 T1:** **Indicators of successful implementation of the core recommendations**^
**a**
^

**Indicator (per included patient)**	**Yes/No**
Recommendation 1: Structured medication counselling	
SMC was performed at least once according to the checklist	Y/N
BBR has been performed at least once	Y/N
Recommendation 2: Use of medication lists	
Patient’s medication list is concordant with physician’s medication list	Y/N
Medication list is consistent with template	Y/N
Patients carry medication list with them	Y/N
Date on medication list not older than 6 months	Y/N
Recommendation 3: Medication checks to reduce PIM	
Medication review was performed according the checklist/MAI score at least once^b^	Y/N

^a^BBR, brown bag review; MAI, Medication Appropriateness Index; PIM, potentially inappropriate medication; SMC, structured medication counselling. ^b^Samsa *et al*.
[11].

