### Data collection methods

Trained study nurses will visit the PCPs twice: at T0 and T1. During the PCP visits, all patients entering the PCP will be asked whether they perceive polypharmacy, whether they carry a medication list with them and whether they have received a medication list from their GP. These data will be collected anonymously by using a tally sheet.

Patient and GP questionnaires will be filled in electronically on the tablet PC in deidentified form. Medication reviews and SMC will be documented by each GP for each patient by using a form on the tablet PC. The data will be stored in a secure central server of the University Hospital Heidelberg. Only project personnel will have access to these data.

GPs will print out or copy the medication lists they have stored in their PCP for each patient at T0 and T1. Additionally, GPs will ask patients to show the medication lists they have with them when the patients give their informed consent (T0) and at T1, copy and deidentify these lists and send them to the study team. If a patient does not have a medication list with him or her, a blank form will be sent.

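### Three of the seven primary indicators are defined by tools described only for the intervention arm, and two of these rest on documentation by unblinded GPs, so the primary difference may partly reflect tool use rather than implementation.

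*Protocol article*

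**What the plan says.** All references are to the protocol article.

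- **Scale.** Under Primary outcome: "The degree of implementation will be expressed by the number of indicators fulfilled per patient included in the study". Table 1 lists seven yes/no indicators, each counting one point.
- **Tool-worded items.** Three of the seven refer to a study tool: "SMC was performed at least once according to the checklist", "Medication list is consistent with template" and "Medication review was performed according the checklist/MAI score at least once". The other four (brown bag review, concordance of patient and physician lists, carrying a list, date of the list) name none.
- **Who gets the checklist.** The section Checklist for SMC and medication reviews says that it "will be handed out to all PCPs of the intervention group and should be used to document each SMC review and each medication review". It adds that the review part is built on the Medication Appropriateness Index (MAI).
- **Who gets the template.** The section Template for medication lists says: "A template for medication lists will be given to each PCP as an adaptable text file". It stands under the heading Intervention study group and asks teams to ensure that their default lists hold the template's information.
- **Control arm.** Usual care study group mentions no special training and a study information leaflet, but no checklist or template.
- **Capture.** Under Data collection methods: "Medication reviews and SMC will be documented by each GP for each patient by using a form on the tablet PC". Medication lists are copied by the GP and sent to the study team.
- **Blinding.** Practices are not blinded; the analysing researchers are.

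**The concern.** The checklist is both a component of the intervention and the yardstick for two of the indicators. The template has the same double role for a third. A control GP who counsels and reviews well in his or her own way may not score on items tied to a tool that the practice is not described as having.

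For counselling and review, the record is also made by someone who knows the allocation. Two further features may widen the gap in recording: the Workshops section trains intervention teams in documentation and tablet use, and under Incentives only intervention practices receive a payment for completing the study.

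At stake is the meaning of the only primary endpoint. The trial asks whether three recommendations are put into practice. The section Recommendations for patients with polypharmacy describes them by content, without requiring a particular study form. The Discussion says that a programme shown to be effective could be offered to about 300 quality circles, so a positive result needs to mean better implementation and not merely use of the tools.

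**Working it through.** **1. Count.** Worded by a study tool: 3 of 7 (43%). Worded by a tool and documented by the GP: 2 of 7 (29%), namely counselling and review. Naming no tool: 4 of 7 (57%). The template item belongs to the first group but not the second, because it can be judged from the list copies.

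**2. The plan's benchmark.** Sample size gives an expected effect of 0.6 SD for the primary outcome, carried over from PIM prescribing. With the stated 3,400 patients and 20 practices per group (170 per practice, 1,700 per quality circle) and ICCs of 0.02 and 0.0008, the design effect is 1 + 169 × 0.02 + 1,530 × 0.0008 = 5.60. The effective size is 3,400 / 5.60 = 607 per arm, and the detectable difference at 80% power is (1.96 + 0.84) × √(2/607) = 0.16 SD. The stated 0.6 is therefore not reproduced. That is a separate matter. Here 0.6 serves only as the effect that the investigators expect.

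**3. How much uptake would give 0.6 SD.** Let k be the number of affected items, u the proportion scoring in the intervention arm, c the proportion in the control arm, and S the SD of the 0–7 count. With no difference on the remaining items, the standardised difference is k(u − c)/S. Setting it to 0.6 gives u − c = 0.6 × S / k. The protocol gives no S, so 1.0 to 2.0 is an assumption. Worst case, c = 0:

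| Assumed S | Points needed (0.6 × S) | k = 3 | k = 2 |
|---|---|---|---|
| 1.0 | 0.6 | 20% | 30% |
| 1.5 | 0.9 | 30% | 45% |
| 2.0 | 1.2 | 40% | 60% |

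**4. Check with S derived from the items.** Assume that the unaffected items are fulfilled by 50% in both arms, that c = 0, and that the correlation between items is 0, 0.2 or 0.4. S is the root of the mean of the two arms' variances. For k = 3 and correlation 0, the control variance is 4 × 0.25 = 1.00. At u = 0.225 the intervention variance is 1.00 + 3 × 0.225 × 0.775 = 1.52. The standardised difference is 3 × 0.225 / √1.26 = 0.60. Across the three correlations, the uptake needed is 23%, 32% and 40% for three items, and 37%, 52% and 64% for two. This agrees with the table.

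**5. When controls do score.** The required quantity is the gap, not the level. With S = 1.5, u = 30% and c = 15%, three items give 3 × 0.15 = 0.45 points, or 0.3 SD: half the expected effect.

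**6. Do existing safeguards remove it?** Blinding the analysts acts after the GP has made the record. Adjustment for baseline need not help, because allocation stays concealed until baseline collection is complete and the tools arrive afterwards. The Discussion acknowledges possible performance bias but does not mention indicators tied to the tools.

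**The case against.** The case on the other side is substantial.

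- **The tools may simply express the recommendations.** The checklist, the template and the review checklist cite the same sources as the recommendations. Acting according to the checklist can be read as covering its content, and the review item also admits the published MAI score. A reader might infer that a control GP without the form must score No; the article does not say so. This stands, but it also leaves open that such a GP will score No, and Table 1 does not settle it.
- **The template item is close to a content test.** Practices need lists that hold the template's information, and a control list may do so. That the template is withheld from controls follows from its placement, not from an explicit statement. This stands.
- **Not all three items are recorded by unblinded GPs.** Only counselling and review are. The template item can be judged from copies, although the unblinded GP collects them and the article does not name the scorer.
- **One form in both arms is possible.** Both arms receive tablets, and the sentence on documentation refers to each GP. It would be wrong to conclude that controls cannot record counselling or reviews.
- **Use of the tools is partly the aim.** The outcome is practice performance, and the Background says that the recommendations are poorly implemented in routine care, so low control scores may be genuine.

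These points limit the size and certainty of the problem. They do not remove the asymmetry in the counselling and review items.

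**Conclusion.** The point holds as a risk of unknown size. Three of seven equally counted indicators are defined by tools described only for the intervention arm, explicitly for the checklist and by placement for the template. Two of them rest on documentation by unblinded GPs. Part of the primary difference may therefore reflect use of the study's tools and forms.

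The 20% to 40% figure (three items) and the 30% to 60% figure (two items) are upper-end illustrations. They rest on zero control scores, no difference on the other items and an assumed SD. They show that moderate uptake could supply the whole expected effect, not that it will.

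A reader might go further and infer that the difference is built in, or that a positive result could arise with no change in care at all. The article does not support that. It would require false recording, or equally good control care that goes unscored, and neither is shown.

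**What to change.** - **Define by content.** Reword the three items in Table 1 using the protocol's own description of the recommendations. Counselling: medicines actually taken inventoried, and adherence and application problems assessed. List: required information items present. Review: MAI criteria considered.
- **Capture alike.** State that counselling and reviews are recorded with the same short form in both arms.
- **Mask the scoring.** State that study-team staff masked to arm score the list copies already being collected.
- **Sensitivity analysis.** Pre-specify the primary comparison on the four indicators that name no study tool. Repeat it without the brown bag review, which the protocol places within counselling and which may therefore also be GP-reported.

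The cost is rewording, one short common form and masked scoring of existing material. There are two downsides: a common form may prompt some control GPs to counsel or review, and the expected difference becomes less favourable. A common form also leaves the recording with unblinded GPs, so it removes the difference in instrument but not the reporting bias. The trial status section describes a planning phase with recruitment of practices begun, so these changes were still feasible.
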